#### Waitlist control group

Participants in the control group will engage in usual care delivered within the nursing home for 14 weeks after the baseline assessment. If the SDTICA program improves cognitive function and psychological indicators after 14 weeks, it will be applied after obtaining the consent of participants in the waitlist control group as compensation for their participation. Moreover, it can reduce the influence of participant expectation on intervention effect.

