
There is robust evidence that interventions guided by motivation theory can have a significant effect on the maintenance of individual behavioural changes [31, 32]. Further, self-determination theory (SDT) is a motivational theory commonly used in behavioural interventions [33]. It emphasises improving autonomy support, which is consistent with the autonomous supportive environment provided by AT [34]. Motivation, which is the initiating factor of individual activities and an important factor in maintaining the continuity of activities, is considered to be the most powerful and stable predictor of activity at the individual level [35]. Meeting the three basic psychological needs of autonomy, competence, and relatedness, and then promoting the generation of internal motivation and the internalisation of external motivation is important for the promotion and maintenance of positive behaviour change in older adults, thereby helping individuals maintain behavioural changes for up to 12 months [36–39].Therefore, this study attempts to apply SDT in the design and implementation of intervention programs for the older adults with MCI in nursing homes, in order to more effectively trigger and maintain participants’ positive behavioural changes.

To these ends, we can reasonably adopt the SDT as a theoretical framework to innovatively develop an integrated art-based intervention for older adults with MCI in nursing homes in China and conduct a methodologically rigorous RCT; moreover, a 6-month follow-up will be conducted to evaluate its short- and long-term effects on neuropsychological outcomes in older adults with MCI. We hypothesized that the 14-week, 27-session SDT-based integrated creative art (SDTICA) program could serve as a non-pharmaceutical intervention to effectively improve cognitive, psychological, and social functioning in older adults with MCI in nursing homes.

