### Sample size determination

The sample size was calculated based on MoCA score improvement reported in our previous study that evaluated the effect of creative expressive therapy on improving cognitive function in patients with MCI [54]. The MoCA scores were 24.68 ± 1.84 (intervention group) and 23.13 ± 1.68 (control group) in our previous study. Using PASS Version 11.0 software (NCSS, Kays-vile, Utah, USA), a sample size of 25 participants per group was determined as being sufficient to detect an effect with a type 1 error rate of 5% (α = 0.05) and 90% power (β = 0.10). To account for clustering, the sample size was calculated according to the requirements of the cluster RCT [55]. Given that interclass correlation coefficient = 0.01 [56], N (individual RCT the required sample size) = 50, “n” means sample size for each cluster, and “k” means number of clusters, the required sample size for each group was calculated. Considering a 15% attrition rate, a total of [(49.5*k)/(0.85*k-0.425)] participants are required.

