### Data collection

Data collection for the outcome variables pertaining to participants with MCI will be performed in nursing homes by trained researchers. Data will be collected at three time points: baseline, after 14 weeks of intervention, and at 24 weeks of follow-up. To reduce the risk of measurement bias, outcome assessors and statistical analysts will be blinded to the intervention and control allocation and will not be involved in the implementation of the intervention. Data will be encoded independently by two research associates, and inconsistencies will be double checked with the data source to ensure data accuracy.

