### Data analysis

The study will be analysed and reported according to the CONSORT statement for cluster RCTs. The data analyses will be performed using IBM SPSS Statistics Version 21.0 software (IBM, Armonk, New York, USA). Demographic and other baseline characteristics will be summarised using descriptive statistics. Continuous variables with normal distribution will be presented as mean ± standard deviation; non-normal variables will be reported as median (interquartile range). The balance of the baseline data of the intervention and control groups will be compared using the two independent samples t-test, Chi-square test, Fisher’s exact test, and Mann-Whitney U rank-sum test. A mixed-effects model accounting for clustering effects will be used to obtain effect estimates, 95% confidence intervals, and p-values for all outcomes; this will demonstrate whether objectively measured neuropsychological test scores improved in the intervention group compared with the control group at 14 and 36 weeks.

In addition, some potential confounders such as age, sex, and education level will be adjusted. To minimize selection bias, statistical analyses will be based on an intention-to-treat (ITT) approach [74], and missing data will be imputed using the multiple imputation method. As a sensitivity analysis, we will perform per-protocol analyses [75], including only the participants who completed the entire intervention process with compliance greater than 80% and outcome assessment at two time points. A value of *P* < 0.05 will be considered significant and the alpha level will be two-sided. Data management will be the primary responsibility of the research team. All data will be securely stored in an electronic database and accessible only to researchers who meet the research ethics approval.

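### The waitlist controls are held on usual care only to week 14, so the later follow-up comparison may become early versus delayed program

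*Protocol article*

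**What the plan says.** Under Waitlist control group, the protocol article states that controls "will engage in usual care delivered within the nursing home for 14 weeks after the baseline assessment". The next sentence gives the crossover rule: "If the SDTICA program improves cognitive function and psychological indicators after 14 weeks, it will be applied after obtaining the consent of participants". The people meant are the controls, and the offer is described as compensation for taking part. It gives no start week and does not mention the follow-up visit.

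Elsewhere the plan relies on a control group after week 14:

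- Background sets the aim: "a 6-month follow-up will be conducted to evaluate its short- and long-term effects on neuropsychological outcomes in older adults with MCI".
- Data collection fixes the assessments at "baseline, after 14 weeks of intervention, and at 24 weeks of follow-up". Table 1 agrees and repeats every primary and secondary outcome at 24 weeks.
- Data analysis will test whether scores "improved in the intervention group compared with the control group at 14 and 36 weeks".

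The Abstract and the Study design section say only that the waitlist group receives usual care, without a duration.

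**The concern.** The control condition is protected to week 14, but the between-group comparison continues to week 24 or 36. In that interval control residents may be given the program. The trigger is a favourable week-14 result, so exposure would occur in just the case where the durability of the benefit is the open question.

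The intention-to-treat contrast at follow-up would remain a randomised comparison, but of a different question: early against delayed program. The long-term effect against usual care, which Background sets out to measure, would no longer be estimated. If the arms converged, a reader could conclude that the benefit fades when controls were partly catching up.

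**Working it through.** **Inputs from the protocol article**

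- Program: 14 weeks, 27 sessions (Abstract).
- Follow-up: week 24 (Table 1, Data collection) or week 36 (Data analysis).
- Effect and spread, from Sample size determination: "The MoCA scores were 24.68 ± 1.84 (intervention group) and 23.13 ± 1.68 (control group) in our previous study". The difference is 24.68 − 23.13 = 1.55.
- Size before cluster and attrition inflation: 25 per group, for 90% power at α = 0.05 (Sample size determination). The test is two-sided (Data analysis).

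**The plan's own figure.** The stated 25 per group is reproduced by the normal-approximation formula, two-sided, with SD 1.68. With the pooled SD, √((1.84² + 1.68²)/2) = 1.762, the same formula gives 28. The power figures below use the pooled SD and the noncentral t distribution, so the undiluted power is 86%, not 90%. That gap has nothing to do with crossover.

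**The window.** From week 14 to week 24 is 10 weeks, in which 10/14 = 71% of the program fits. From week 14 to week 36 is 22 weeks, in which all of it fits.

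**Dilution.** These assumptions are not in the documents: the 1.55-point effect persists in the intervention arm, benefit builds linearly over 14 weeks, and controls gain at the same pace. Then

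difference at follow-up = 1.55 × (1 − u × e/14),

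where u is the share of controls taking up the program and e is the number of program weeks they have had: follow-up week − 14 − delay, kept between 0 and 14. Sessions received are 27 × e/14.

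Week 24:

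| Delay after week 14 | e (sessions) | u = 100%: difference, power | u = 50%: difference, power |
|---|---|---|---|
| 0 weeks | 10 (19.3) | 0.44, 14% | 1.00, 50% |
| 4 weeks | 6 (11.6) | 0.89, 41% | 1.22, 67% |
| 8 weeks | 2 (3.9) | 1.33, 74% | 1.44, 81% |
| 10 weeks or more | 0 (0) | 1.55, 86% | 1.55, 86% |

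Example, 4-week delay and full uptake: 1.55 × (1 − 6/14) = 0.89.

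Week 36: any start within 8 weeks of week 14 leaves at least 14 weeks, so controls can finish. The difference is 1.55 × (1 − 1) = 0 at full uptake and 1.55 × (1 − 0.5) = 0.78 at half uptake.

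**Sensitivity to the SD.** With SD 1.68, power for differences of 1.55, 1.00 and 0.44 is 89%, 54% and 15%. The pattern does not change. These powers use the 25 per group that applies before clustering. The article inflates recruitment for an intraclass correlation of 0.01 and 15% attrition, so 25 serves as the effective size.

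**The case against.** The strongest reply is that the text is silent on timing and does not call for early crossover. The words about week 14 may say when benefit is judged, not when controls start. Compensation for participation can mean something given once participation, including the follow-up visit, is over. Data analysis describes one mixed model for both time points and no interim analysis, and Data collection keeps assessors and analysts blinded. Acting on a week-14 result would sit badly with both.

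An immediate start is also unlikely. The data must be double-encoded and analysed, consent obtained, and two instructors, two social workers and a care worker found for the sessions. A 10-week delay removes the dilution at week 24 altogether. Fig. 1 or the Additional file may settle the order. The week-36 figures depend on a separate inconsistency about the follow-up date.

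Much of this stands. The start date is an inference, the zero-delay row is close to a worst case, and the sizes rest on assumptions. But no visible text delays the offer, and the one duration given for usual care ends at week 14. A crossover rule tied to the week-14 result, beside a planned later comparison with the same controls, is a badly fixed rule and not merely a detail left to a fuller document.

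**Conclusion.** The concern holds, with medium confidence, and should be fixed. As written, the plan permits controls to be exposed before follow-up when the program succeeds, which pulls the follow-up contrast towards zero. Under the assumptions of persistence, linear build-up and equal pace, the week-24 MoCA difference lies between 1.55 (start delayed 10 weeks or more) and 0.44 (immediate start, full uptake). Power runs from 86% down to 14%. If follow-up is at week 36, a start within 8 weeks leaves 0.78 at half uptake and nothing at full uptake.

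The week-14 comparison is sound. If the intention is already to wait, the defect is one of wording, and the effect on the results disappears once the text says so.

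**What to change.** Add to Waitlist control group: *Control homes remain on usual care until their last follow-up assessment is complete; the program is offered to them only after that.* Settle whether that assessment is at week 24 or week 36. Keep week-14 results by arm from outcome assessors and home staff until the follow-up data are locked. Staff will know their home's allocation, but they need not know the results.

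If the offer cannot wait, decide the following now, whatever week 14 shows:

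- Name week 14 as the confirmatory comparison.
- Keep the follow-up intention-to-treat contrast, labelled as early versus delayed program.
- Report how many controls had started and how many sessions they had received.
- Remove the long-term claim against usual care from Background.

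The cost is protocol wording, plus a wait for controls about 10 weeks longer (24 − 14), or 22 weeks (36 − 14) if follow-up is at week 36. Under the alternative, the cost is a narrower long-term claim.

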### Outcome measures

To explore the effects and mechanisms of the SDTICA program, various measurements will be obtained at baseline and immediately after the intervention. Outcome measures mainly include neuropsychological assessments. All outcome measures and assessment time points are shown in Table 1.

**Table 1 Tab1:** SDTICA study outcome measures

Measures/Time point	Screening	Baseline	Post-intervention	Follow-up
		0 weeks	14 weeks	24 weeks
Eligibility assessment				
Diagnostic criteria	×			
Inclusion criteria	×			
Exclusion criteria	×			
**Informed consent**	×			
**Demographic characteristics**		×		
**Neuropsychological assessment**				
**Primary outcomes**				
General cognitive function (MoCA, MMSE)		×	×	×
Psychological indicators (GDS, SAS, MUNSH, GNSS, and QoL-AD)		×	×	×
**Secondary outcomes**				
Verbal memory (AVLT)		×	×	×
Language (CVFT and BNT)		×	×	×
Executive function (DST and STT)		×	×	×
Visuospatial skill (CDT)		×	×	×
Social function (FAQ and LSNS)		×	×	×
Physiological function (ADL)		×	×	×
**Qualitative outcome evaluation**			×	×

×, Time point in the trial at which the assessment will take place. MoCA, Montreal cognitive assessment; MMSE, Mini-Mental State Examination; GDS, Geriatric Depression Scale; SAS, Self-Rating Anxiety Scale; MUNSH, Memorial University of Newfoundland Scale of Happiness; GNSS, General Needs Satisfied Scale; QoL-AD, Quality of life-Alzheimer’s disease; AVLT, Auditory Verbal Learning Test; CVFT, Category Verbal Fluency Test; BNT, Boston Naming Test; DST, Digit Span Test; STT, Shape Trail Test; CDT, Clock Drawing Test; FAQ, Functional Activities Questionnaire; LSNS, Lubben Social Network Scale; ADL, Activity of Daily Living

#### Demographic characteristic measurements

Demographic characteristics (e.g., age, sex, marital status, education level, and socioeconomic status), medical history, usage of drugs, and leisure activities will be collected at baseline.

#### Neuropsychological assessments

##### Primary outcome

The primary outcomes, which include global cognitive function and psychological indicator, will be measured using the MoCA, MMSE, Geriatric Depression Scale [62], Zung Self-Rating Anxiety Scale [63], General Needs Satisfied Scale [64], Memorial University of Newfoundland Scale of Happiness [65], and Quality of life-Alzheimer’s disease questionnaire [66].

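### Seven unranked primary scales at two time points, each tested at two-sided 0.05 with no success rule, do not hold the 5% type 1 error at which the trial was sized on MoCA alone

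*Protocol article*

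**What the plan says.** The section on the primary outcome gives one flat list: "The primary outcomes, which include global cognitive function and psychological indicator, will be measured using the MoCA, MMSE, Geriatric Depression Scale [62", then the Zung anxiety scale, GNSS, MUNSH and QoL-AD. Table 1 agrees. Its primary block has one row for MoCA and MMSE and one for "Psychological indicators (GDS, SAS, MUNSH, GNSS, and QoL-AD", with both rows marked at post-intervention and at follow-up.

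The Data analysis section promises "effect estimates, 95% confidence intervals, and p-values for all outcomes" from a mixed-effects model, to show whether scores "improved in the intervention group compared with the control group at 14 and 36 weeks". The only decision rule is that P < 0.05 "will be considered significant and the alpha level will be two-sided".

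The sample size section rests on one scale: "The sample size was calculated based on MoCA score improvement reported in our previous study". It uses a "type 1 error rate of 5% (α = 0.05) and 90% power (β = 0.10").

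The follow-up week is inconsistent. Data collection lists "baseline, after 14 weeks of intervention, and at 24 weeks of follow-up", whereas Data analysis says 36 weeks. That needs reconciling, but there are two post-baseline time points on either reading.

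**The concern.** A 5% type 1 error describes one test. Here seven scales at two times give up to 7 × 2 = 14 tests that carry the primary label, each with its own 5% chance of rejecting when there is no effect. Nothing says which result, or which combination, decides whether the trial has succeeded. A report could therefore follow the plan to the letter and present whichever of the fourteen reached significance as a positive primary finding.

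The sample size assumes a single MoCA comparison, so the error rate and power it quotes describe a narrower claim than the one the outcome section sets up.

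This is more than detail awaiting an analysis plan. The article itself fixes the unranked primary list and the flat threshold, and a later plan could rank the scales only by departing from it.

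**Working it through.** **Inputs from the protocol article**
- Primary scales: 7 (Primary outcome section, Table 1).
- Post-baseline time points: 2 (Table 1, Data analysis).
- Threshold: 0.05 two-sided (Data analysis).
- Sizing: MoCA 24.68 (SD 1.84) against 23.13 (SD 1.68), 90% power, 25 per group before clustering (Sample size determination).

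**Assumed, because the article gives no values:** correlations between scales and between time points, and the rule that any one significant scale makes a positive result.

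**1. The plan's own figure.** The difference is 24.68 − 23.13 = 1.55. With n = 2(1.960 + 1.282)²·SD²/1.55²:
- control SD 1.68: n = 24.7, rounded up to 25 per group;
- pooled SD √[(1.84² + 1.68²)/2] = 1.762: n = 27.2, rounded up to 28 per group.

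So the stated 25 is reproduced with the control-group SD, for one MoCA test at alpha 0.05. No allowance is made for a second primary test.

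**2. One time point, seven tests, no true effect.** If independent, 1 − 0.95⁷ = 0.302. With a common between-scale correlation ρ, the chance is 1 − ∫φ(u)·[Φ((1.96 − √ρ·u)/√(1−ρ)) − Φ((−1.96 − √ρ·u)/√(1−ρ))]⁷ du:

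| ρ | Chance of at least one rejection |
|---|---|
| 0 | 30.2% |
| 0.5 | 23.0% |
| 0.7 | 17.8% |
| 0.8 | 14.9% |

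**3. Both time points, fourteen tests.** If independent, 1 − 0.95¹⁴ = 0.512. This is an upper bound, since repeat measurements of one scale on the same people are correlated. Simulation (400,000 replicates, separate correlations between scales and between times) gives:

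| Between scales | Between times | Chance of at least one rejection |
|---|---|---|
| 0.5 | 0.5 | 38.2% |
| 0.5 | 0.7 | 35.5% |
| 0.7 | 0.7 | 28.0% |
| 0.8 | 0.8 | 22.0% |

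**4. Benefit only.** Steps 2 and 3 count rejections in either direction. Counting only false claims of benefit at one time point gives 16.2% (ρ = 0), 11.5% (0.5), 8.9% (0.7) and 7.4% (0.8), against a nominal 2.5%.

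**5. Cost of keeping all seven primary.** Bonferroni at one time point uses 0.05/7 = 0.00714 per test. MoCA would then need 38 per group (control SD) or 41 (pooled SD) before clustering. If 25 per group is kept, MoCA power falls as follows:

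| SD and method | Power at 0.05 | Power at 0.05/7 |
|---|---|---|
| Control SD, normal approximation | 90% | 72% |
| Control SD, t-test | 89% | 67% |
| Pooled SD, normal approximation | 88% | 66% |
| Pooled SD, t-test | 86% | 62% |

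**The case against.** The strongest reply is that the rule under which any one scale suffices is not in the protocol, and that the article's own wording points to benefit in both domains. The hypothesis in the Background covers cognitive, psychological and social functioning together. The section on the waitlist control group makes the later offer of the programme depend on improvement in both cognitive function and psychological indicators at 14 weeks. Suppose success required at least one of the two cognitive scales and at least one of the five psychological scales at 14 weeks. The error rate under no effect at all would then be 2.2% (independent), 4.4% (ρ = 0.5), 5.4% (0.7) or 5.7% (0.8), which is close to nominal.

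That calculation stands, and it shows that the size of the problem depends on the success rule. It does not rescue the plan:
- The waitlist condition decides only whether controls are offered the programme, and it does not say which scales must succeed.
- Even as a success rule it would not protect the mental-health claim. If cognition truly improved, five psychological scales at one time point would still give a false rejection with probability 1 − 0.95⁵ = 22.6% if independent, or 18.3% at ρ = 0.5.
- Sizing on MoCA alone does not establish 90% power for a joint claim. The same holds if all seven scales had to succeed, although type 1 error would then not inflate.

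A reader might also infer that the true error rate is 51%. The article does not support that as an estimate, because it treats two measurements of one scale on the same people as independent. Nor is the entry restriction on MMSE (24–30) a separate argument against its primary status. The restriction applies only at entry, and MoCA is also truncated there by the education-specific cutoffs.

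Multiplicity methods are often left to an analysis plan, which is not shown here. That is a fair reason not to fault the missing method alone. The fault lies in the unranked list and the flat threshold, which the article does state.

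**Conclusion.** The concern holds. With seven unranked primary scales, two time points and one unadjusted threshold, the stated 5% type 1 error does not describe the trial's primary claim, and the sample size supports only the MoCA part of it.

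If any one significant scale counts as positive, the chance of at least one false rejection in either direction under no effect is about 15–30% at one time point (between-scale correlation 0.8 to 0). It is about 22–38% over both (between-scale and between-time correlations 0.5 to 0.8). The correlations and that success rule are assumptions. A strict joint rule could bring the error under no effect near 5%, but the article states no such rule and is not sized for one. The primary claim should be settled before any unblinded analysis.

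**What to change.** Name MoCA at 14 weeks, the end of the intervention and the scale on which the trial is sized, as the single primary outcome. Make MMSE, GDS, SAS, GNSS, MUNSH, QoL-AD and every follow-up value secondary.

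If a formal mental-health claim is wanted, name one psychological scale in advance and test it at two-sided 0.05 only if MoCA is significant. This fixed sequence holds the overall error for the two claims at 5%. For the remaining outcomes, either apply Holm or state that they carry no error control.

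The change means rewording the Abstract methods, Table 1, and the Primary outcome and Data analysis sections, as a dated amendment. The registry record was not available; if it lists the same seven primary outcomes, it needs the same amendment. No participants are added and MoCA keeps its full alpha, so no MoCA power is lost. The price is that the psychological scales lose primary status in a trial that aims at both cognition and mental health. The optional second step softens that for one scale only.
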